## Methods/design

### Study design

The ADD study is a multicentre parallel group, double-blind, randomised, placebo-controlled superiority trial of augmentation of serotonergic antidepressants with metyrapone in patients with moderate to severe depression who have failed to respond to adequate trials of at least two antidepressants in their current episode.

### Study population

The initial study aim was to recruit 190 patients. However due to initial slow recruitment rates after discussion with the funder, sponsor and the independent Data Monitoring and Ethics Committee, a revised target of 140 was agreed by accepting a reduction in power of the study from 90% to 80% on the primary outcome measure (see below). These patients will be recruited from primary and secondary care settings.

### Inclusion criteria

•Diagnostic and Statistical Manual of Mental Disorders – Fourth Edition (DSM-IV) [61] defined major depressive episode assessed using the Structured Clinical Interview for DSM (SCID) research version [62].

•Hamilton Depression Rating Scale -17 item (HDRS17) [63] score of ≥ 18 at week -2 and 0 (see below).

•Massachusetts General Hospital Treatment Resistant Depression (MGH-TRD) staging score of 2-10 as a measure of treatment refractoriness [64]. This cut off is based on MGH-TRD scores seen in primary and secondary care, but short of tertiary care, in the UK NHS [65].

•Single agent or combination antidepressant treatment which includes a serotonergic drug (a selective serotonin reuptake inhibitor, a tertiary amine tricyclic, venlafaxine, duloxetine or mirtazapine). At the point of randomisation, patients must have been on their current antidepressant medication, at the current dose, for a minimum of four weeks.

•Aged between 18-65. An upper age limit is included to reduce rates of physical health comorbidities that could complicate decisions around the safety of prescription of a drug (metyrapone) that may lower cortisol levels.

### Exclusion criteria

•Other DSM-IV axis I diagnosis, other than an anxiety disorder considered to be secondary to a primary diagnosis of depression, confirmed using SCID.

•Physical co-morbidity that would make metyrapone inappropriate, including untreated hypothyroidism, disorders of steroid production, cardiac failure, angina, myocardial infarction in the last 3 years and renal failure.

•Pregnancy or breastfeeding.

•Use of medication that would interfere with metyrapone.

•Dependence on alcohol or other drug(s) in the past 12 months, and/or current harmful use of such substances (defined as meeting SCID criteria for harmful use or dependence).

•Recent participation in a research study that could interfere with results.

### Recruitment

Patient identification will occur across two hubs of the UK NIHR Mental Health Research Network - the North East with centres in Newcastle and Teesside and the North West with Manchester as the centre - and in the West Yorkshire Comprehensive Local Research Network – with centres in Leeds and Bradford. Potential participants will be identified through routine clinic appointments at study sites and Participant Identification Centres that will include Primary Care and Community Mental Health Teams.

### Intervention

Participants will continue their existing antidepressant regime. Randomisation will be in a 1:1 ratio of metyrapone to matched placebo using permuted block randomisation, stratified by inclusion in mechanistic studies sub-sample, level of care setting (i.e. primary or secondary care) and by centre. A randomisation code will be computer generated by the Newcastle Clinical Trials Unit and coded packs of the study drug and matched placebo will be produced, according to the randomisation schedule. All medication will be supplied from a single central pharmacy with all participants and study staff blinded to treatment allocation. To ensure blinding the metyrapone will be over-encapsulated and the placebo will be visually identical. Participants in the treatment arm will receive study drug (metyrapone 500 mg or placebo) twice daily, prescribed in the morning and at noon, for 21 days. Adherence to medication will be assessed using measures of 11-deoxycortisol as described below under “HPA axis Assessment”.

Apart from treatment with the experimental intervention, all other treatments will remain under the control of the patient’s normal treating psychiatrist and/or general practitioner. However, the patients’ clinicians will be encouraged to avoid changes to medications between enrolment (week -2) and the primary outcome time point (week +5) unless there is a compelling clinical reason to alter treatment. All current medication will be recorded at all follow up time points.

### Objectives

#### Primary clinical objective

•The primary objective is to determine whether metyrapone (500 mg twice a day) for 21 days is efficacious in augmenting conventional serotonergic antidepressants in TRD in a UK NHS primary and secondary care setting. This to be assessed by Montgomery-Åsberg Depression Rating Scale (MADRS) [66] scores two weeks post treatment (week +5 from randomisation), comparing patients treated with metyrapone to those treated with placebo.

#### Secondary clinical objectives

•To determine the clinical effect size at two weeks post-completion of treatment of a three-week course of metyrapone (vs placebo) augmentation of antidepressants in depressed patients who have failed to respond to at least two courses of antidepressants, in primary care and psychiatric outpatient clinics in the UK.

•To assess whether the response is sustained for up to 21 weeks post cessation of metyrapone.

•To assess whether metyrapone augmentation improves patients’ quality of life using the self-completed EuroQol EQ-5D instrument (http://www.euroqol.org/).

•To assess the tolerability and safety of metyrapone augmentation in a large sample taken from a representative population of psychiatric outpatients and primary care patients with TRD.

#### Mechanistic objectives related to the full RCT sample

•To assess whether metyrapone changes patients’ HPA axis function.

•To assess whether changes in HPA axis function with metyrapone persist after stopping metyrapone.

•To assess whether the change in HPA axis function correlates with clinical response.

•To assess whether baseline HPA axis function predicts clinical response.

### Study schedule

All assessments will be undertaken by trained research personnel under the supervision of the clinically trained principle investigators ([name]).

#### Screening visit (week -2)

Written informed consent will be obtained and study eligibility determined. Height, weight and safety measurements (see Table 2 for details) will be recorded. Baseline blood tests including urea and electrolytes, cortisol, thyroid function test, liver function tests, full blood count and β-human chorionic gonadotropin (if indicated) will be taken. Background factors, personality, and childhood adversity and life events will be assessed between recruitment and randomisation, using the NewMood background questionnaire [67] given to patients to complete and return at the next visit. This questionnaire includes the Big Five Inventory 44 personality questionnaire [68], a negative life events questionnaire adapted from the list of Life Threatening Experiences [69], the Social Circumstances Questionnaire, which is an adaptation of the Social Support Questionnaire [70] as used in the NewMood study [67], the Childhood Trauma Questionnaire [71] and the Ruminative Responses Scale [72]. Depression severity will be determined using the HDRS17, which will be rated using the GRID-HAMD for improved reliability [73], and the MADRS [66].

**Table 2 T2:** Schedule of assessments

	**Enrolment**	**Randomisation**	**Follow up**							
**Time point**	**Week-2**	**Week 0**	**Week 1**	**Week 2**	**Week 3**	**Week 4**	**Week 5**	**Week 8**	**Week 16**	**Week 24**
Assessment of eligibility	√									
Informed Consent	√									
Assessment of baseline characteristics – NewMood questionnaire*	√									
Experimental Intervention										
Assessment of depression severity – HDRS17^1^	√	√								
Assessment of Clinical symptoms – MADRS^2^, CAS^3^, BDI^4^,STAI^5^, YMRS^6^		√			√		√	√	√	√
Assessment of Quality of Life – EQ-5D		√			√		√	√	√	√
Assessment of side effects – TSES^7^		√			√		√	√		
Assessment of side effects and adverse events – self report		√	√	√	√	√	√	√	√	√
Suicide risk assessment	√	√	√		√		√	√	√	√
Pregnancy Test if indicated	√	√	√	√	√					
Assessment of concomitant medication	√	√	√	√	√	√	√	√	√	√
Measurement of HPA axis function (CAR plus 11 pm saliva sample)		√			√		√			
Physical observations**	√***		√				√			
Blood Tests – U&E’s, cortisol	√****		√				√			

* - See text under “Screening Visit” for description of NewMood questionnaire details.

** - Physical observations comprised sitting and standing pulse and blood, and pressure respiration rate.

*** - Screening physical observations also included height and weight.

**** – Screening blood tests also including thyroid function tests, liver function tests and full blood count.

^1^*HDRS17* Hamilton Depression Rating Scale – 17 item.

^2^*MADRS* Montgomery-Asberg Depression Rating Scale.

^3^*CAS* Clinical Anxiety Scale.

^4^*BDI* Beck Depressive Inventory.

^5^*STAI* State Trait Anxiety Inventory.

^6^*YMRS* Young Mania Rating Scale.

^7^*TSES* Toronto Side Effects Scale.

#### Randomisation visit (week 0)

Subjects will excluded if their HDRS17 has dropped below 18 or if there has been any change in their current antidepressant medication (drug or dose). Otherwise study medication will be supplied to commence the following day.

#### Follow –up

Data will be collected at weeks +1, +2, +3 (end of active treatment period), +4, +5 (primary outcome time point), +8, +16 and +24 from the date medication was started (+/- 2 days). The week +2 and +4 visits can be completed by telephone. Details of the assessments at each time point are described in Table 2. Depression severity will be assessed using the MADRS administered by trained members of the research team at time +3, +5,+8, +16 and + 24 weeks. The primary outcome measure will be the change in MADRS from week 0 to +5 weeks. The MADRS has preferable psychometric properties and higher sensitivity to change than other depression rating scales [74] and was associated with the largest effect size in the Jahn study [33]. Additional secondary outcome measures of symptomatology (Clinical Anxiety Scale (CAS) [75], Beck Depressive Inventory (BDI) [76], State Trait Anxiety Inventory (STAI) [77] and Young Mania Rating Scale (YMRS) [78]) will be conducted at the same time points as described for the MADRS. Quality of life will be assessed using the self-completed EuroQol EQ-5D instrument (http://www.euroqol.org/) and tolerability using the Toronto Side Effects Scale (TSES) [79].

Metyrapone treatment potentially engenders hypocortisolaemia with manifestations including a risk of postural hypotension, hyperkalaemia and hypernatremia. Therefore, safety assessments will include serum cortisol measures at week +1 as well as measuring sitting and standing blood pressure and urea and electrolytes at weeks +1 and +5.

### HPA axis assessment

Cortisol levels to determine the cortisol awakening response (CAR) [80] will be obtained at the start of treatment (week 0) and then again at +3 and +5 weeks for all patients. This entails participants collecting 5 ml of saliva by passive drool [81] into a plastic collecting tube on wakening and then again at 15 minute intervals for a further hour. A total of five samples will be collected on each occasion either the day before or day after the planned study visit. Participants will also be asked to collect a saliva sample for cortisol assay at 11 pm the night before each of the three CAR assessments. In addition to collection of saliva samples, participants will complete a brief questionnaire relating to the nature and quality of sleep the night before the CAR assessment.

In addition to the saliva samples, serum samples will be taken at -2, +1 and +5 weeks for analysis of cortisol precursors and metabolites. Metyrapone administration has previously been shown to cause an increase in levels of ACTH, DHEA and 11-deoxycortisol together with an increase in the cortisone:cortisol ratio [33,82]. The increase in 11-deoxycortisol between weeks -2 and +1 will be used as a measure of adherence to medication since this has been shown to be highly sensitive to treatment with metyrapone [33,82].

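### The rule allowing saliva sampling the day before or after a visit lets the baseline CAR fall on the first dosing day and the week +3 samples fall a day or more after dosing has ended

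*Protocol article*

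**What the plan says.** Four sections of the protocol article fix the relevant dates.

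- **HPA axis assessment.** The CAR "will be obtained at the start of treatment (week 0) and then again at +3 and +5 weeks for all patients". On the sampling day: "A total of five samples will be collected on each occasion either the day before or day after the planned study visit". Five saliva samples are taken from waking over one hour. A further sample is taken at 11 pm on the evening before each CAR.
- **Randomisation visit (week 0).** "Otherwise study medication will be supplied to commence the following day".
- **Intervention.** Study drug is given "twice daily, prescribed in the morning and at noon, for 21 days".
- **Follow-up.** Visits are counted "from the date medication was started (+/- 2 days" either way, and week +3 is labelled "3 (end of active treatment period".

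Table 2 schedules saliva at weeks 0, 3 and 5 only. Serum is taken at weeks -2, +1 and +5. The Statistical analysis section names the CAR and the 11 pm cortisol as the measures of whether metyrapone changes HPA axis function, and asks separately whether a change from baseline is still present two weeks after treatment.

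**The concern.** Each rule is reasonable alone, but together they let the sampling day cross both ends of the dosing period.

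At the start, one of the two permitted baseline days is the first day of study drug. A baseline taken after a capsule would be altered by drug in the metyrapone arm only. That is a systematic difference between arms rather than noise, and it would enter every analysis that uses the baseline CAR: change during treatment, change at week +5, and baseline as a predictor of response.

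At the end, two participants who both follow the protocol can give week +3 samples in different drug states. Week +3 is the only saliva occasion between baseline and the post-treatment assessment at week +5, so no other saliva sample can show the on-treatment effect. Serum at week +1 gives on-treatment biochemistry, but not the CAR or the 11 pm saliva value on which the analysis rests. Off-drug samples would tend to dilute the on-treatment contrast.

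**Working it through.** The plan gives no figure to reproduce; the check is calendar arithmetic.

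**Day numbering.** Week-0 visit = day 0. First dose = day 1 (Randomisation visit). Last dose = noon on day 21 (Intervention). Week +3 visit = day 1 + 21 = day 22, window days 20 to 24 (Follow-up). CAR day = visit day - 1 or visit day + 1. The 11 pm sample is on the evening of CAR day - 1 (HPA axis assessment).

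**Baseline.** Permitted CAR days are 0 - 1 = day -1 and 0 + 1 = day 1. Day 1 is the first dosing day. The 11 pm sample falls on day -2 or day 0, before any dose in both cases.

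**Week +3, literal reading.**

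| Visit day | CAR the day before | CAR the day after |
|---|---|---|
| 20 | 19 | 21 |
| 21 | 20 | 22 |
| 22 | 21 | 23 |
| 23 | 22 | 24 |
| 24 | 23 | 25 |

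Of the 10 combinations, 4 fall on or before day 21, 2 on day 22, and 4 on day 23 or later.

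**Time since the last noon dose**, assuming waking at 07:00. For a CAR on day d > 21 it is (d - 21) × 24 - 5 hours. For the paired 11 pm sample it is (d - 22) × 24 + 11 hours.

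| CAR day | CAR, hours after last dose | Paired 11 pm sample, hours after last dose |
|---|---|---|
| 22 | 19 | 11 |
| 23 | 43 | 35 |
| 24 | 67 | 59 |
| 25 | 91 | 83 |

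During treatment a pre-dose waking sample is also 19 hours after the previous noon dose, and an 11 pm sample is 11 hours after it. Day 22 therefore matches a treatment morning in exposure. The clear departure starts at day 23, for the CAR and its paired 11 pm sample alike.

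**Other readings of week +3** (CARs on day 23 or later):

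- Day 22, no window: 1 of 2 (day 23).
- Day 21 ± 2 days (CAR days 18 to 24): 2 of 10.
- Day 21, no window: 0 of 2.

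**Week +5.** Day 1 + 35 = day 36. With the window and the sampling rule, CAR days run from 33 to 39, which is 12 to 18 days after the last dosing day.

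**Illustration of the dilution.** Let p be the share of samples taken off drug and r the share of the on-treatment effect remaining in them. The observed contrast is then the true contrast × [1 - p(1 - r)]. With p = 0.4 it lies between 0.6 (r = 0) and 1.0 (r = 1) of the true value; with p = 0.2, between 0.8 and 1.0. The documents give neither p nor r.

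**The case against.** A reader might infer that most week +3 samples are off drug, since 6 of 10 permitted CAR days fall after day 21. The documents do not support this. That count needs the literal day-22 reading, the full visit window, equal likelihood of all combinations, and day 22 treated as off drug although its waking sample has the exposure of any treatment morning. The day-21 reading is arguable: the Follow-up section calls week +3 the end of active treatment, and the primary objective counts weeks from randomisation. On that reading only 4 of 10 fall after day 21. Sampling is also tied to the planned visit, so adding the window is open to debate.

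A reader might also infer that persistence cannot be separated from the on-treatment effect. Persistence is tested at week +5 against baseline, so week +3 timing does not enter it. Nor does the protocol describe a rebound.

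The baseline problem is a possibility, not a demonstrated fact. It needs the day-after option and a capsule within an hour of waking. The article says only that a capsule is due in the morning, and the order of capsule and saliva tubes may be set in the full protocol or the kit instructions, which are not shown. The documents also do not say how much one capsule alters cortisol within that hour.

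These points limit the size. What stands is that the stated sampling rule permits both overlaps, which is a conflict between stated rules rather than omitted detail.

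**Conclusion.** The point holds in limited form. As written, the rule permits a baseline CAR on the first dosing day, post-dose in the metyrapone arm if the capsule comes within the sampling hour. It also permits week +3 saliva after at least one full day without drug: 4 of 10 combinations on the literal reading, 2 of 10 if week +3 is dosing day 21 with the window. It disappears only if week +3 is day 21 with no window at all. Even a visit exactly on day 22 leaves day 23 as one of its two options.

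The counts are of permitted combinations and do not predict how often each would occur. The hours assume waking at 07:00. The consequence is confined to the mechanistic HPA axis objectives, of which the prediction of response is already labelled exploratory. The MADRS primary outcome and the week +1 adherence measure are unaffected. The week +5 comparison is affected only through a contaminated baseline CAR, if one occurs. It is worth correcting because the remedy is specific and nearly free, and samples without recorded timing could not be reliably separated afterwards.

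**What to change.** Reconcile the sampling sentence under HPA axis assessment with the Intervention, Randomisation visit and Follow-up sections:

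- Complete the baseline CAR before the first capsule, either on the day before the visit or on day 1 ahead of the first dose. The baseline 11 pm sample needs no change.
- Schedule the week +3 CAR so that its preceding 11 pm sample falls on a dosing day, which means a CAR no later than waking on day 22.
- Record the date and time of each sample relative to the last capsule.
- Run a sensitivity analysis that excludes samples outside these limits.

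The cost is a revised sentence, a kit instruction and slightly less flexibility for participants. Only saliva collection changes; dosing does not. If the full protocol or the kit instructions already impose these limits, it is enough to align the article's sentence with them.

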### Sample size, power and effect size

The primary outcome measure is change in MADRS between weeks 0 and +5. The effect size for this measure in the Jahn study [33] was 0.63. The study has been powered around the more conservative moderate effect size of 0.5 which, assuming a post-intervention standard deviation of 12 points [33], corresponds to a six point difference on the MADRS. An achieved sample size of 85 per group is required to detect effect size of 0.5 with 90% power, assuming alpha = 0.05. Allowing for 10% attrition during the trial, the original aim was to randomise 95 per group; 190 in total. However, as described above the recruitment target has been modified accepting a power of 80%, requiring a sample size of 63 per group. Again allowing for 10% attrition during the trial, we aim to randomise 70 per group; 140 in total.

### Statistical analysis

A full Study Analysis Protocol will be drawn up prior to completion of the study and breaking of the study blind.

There is no planned interim analysis and no “stopping rules” for the study as a whole. Individual patients will be withdrawn from the study medication if it appears that to continue would be deleterious for their mental health or safety. This can be determined by the patient, the treating clinician and/or the research team and will be supported by the use of the MADRS particularly if there is an increase in the score for question 10 “suicidal thoughts”, or a lack of improvement in total MADRS score.

The primary outcome will be an intention to treat analysis of variance of the MADRS scores of the two treatment groups (metyrapone and placebo) at +5 weeks covarying for baseline MADRS. The persistence of change in the MADRS score will then be assessed using repeated measures analysis of variance utilising data from all time points. The change and persistence of the change in other clinical and quality of life measures will be examined using the same methods. Additional secondary outcomes will include rates of response (defined as a 50% or greater reduction in MADRS score) and remission (defined as MADRS ≤ 10) with metyrapone versus placebo.

With regard to the mechanistic objectives, the study will examine whether treatment with metyrapone leads to a change in HPA axis function (assessed by examining the CAR and 11 pm cortisol measures) and whether changes in HPA axis function, compared to baseline, are seen two weeks post treatment. Both baseline HPA axis function and change in function with treatment will be assessed to see if they predict clinical response to metyrapone defined by the change in MADRS between week 0 and week +5, in an exploratory analysis.

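### The stated primary ANCOVA names only baseline MADRS although randomisation is stratified by three factors; if those factors are prognostic, the test is mildly conservative and some precision is given up

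*Protocol article*

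**What the plan says.** In the protocol article, the Intervention section describes equal allocation to the two arms in permuted blocks and lists three factors for the strata, in these words: "stratified by inclusion in mechanistic studies sub-sample, level of care setting (i.e. primary or secondary care) and by centre". The Recruitment section names five centres: "the North East with centres in Newcastle and Teesside and the North West with Manchester as the centre", plus Leeds and Bradford in West Yorkshire.

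The Statistical analysis section gives the primary analysis as an intention-to-treat analysis of variance of MADRS in the two groups ("metyrapone and placebo) at +5 weeks covarying for baseline MADRS"). Baseline MADRS is the one covariate named. The same section applies the same methods to the other clinical and quality-of-life measures. None of the three stratification factors appears in any model in the article. The section also announces a full analysis plan, to be written before the study is completed and unblinded; it is not shown.

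The sample size section was "powered around the more conservative moderate effect size of 0.5" and, after the recruitment target was cut, proceeds by "accepting a power of 80%, requiring a sample size of 63 per group".

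**The concern.** Blocking within strata forces the arms to be nearly balanced on centre, care setting and sub-sample. Differences in outcome between strata therefore largely drop out of the treatment contrast. A model without the strata still counts those differences as residual error, so its standard error describes a less precise trial than the one that was run. Confidence intervals come out too wide and p-values too large.

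Whether this matters depends on whether the strata predict week +5 MADRS once baseline is accounted for. The documents offer no figure. It is plausible that they do: care setting may reflect position in the treatment pathway, MADRS is rated by local research staff who may differ between centres, and the sub-sample has an upper age limit of 60 against 65 for the trial. At stake is precision that the design has already secured, in a trial that lowered its target power from 90% to 80%.

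**Working it through.** **Inputs from the article:** SD 12 and difference 6 ("assuming a post-intervention standard deviation of 12 points [33], corresponds to a six point difference on the MADRS"); alpha 0.05, taken as two-sided; 63 analysed per arm; 10% attrition; 140 randomised; five centres.

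**Assumed, not in the documents:** q, the share of residual week +5 variance explained by the strata, from 0 to 0.20; rho, the correlation of baseline with week +5 MADRS, from 0 to 0.5.

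**Step 1: reproduce the plan's figures.** n per arm = 2(z_0.975 + z_power)² (SD/difference)².
- 80% power: 2(1.960 + 0.842)² × (12/6)² = 62.8, so 63; 63/0.9 = 70 per arm, 140 in total.
- 90% power: 2(1.960 + 1.282)² × 4 = 84.1, so 85; 85/0.9 = 94.4, so 95 per arm, 190 in total.

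Both agree with the article. Power at 63 per arm is 80.1% by the normal approximation and 79.5% by the noncentral t. The calculation is for an unadjusted two-group comparison and takes no credit for baseline or strata.

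**Step 2: effect of omitting the strata.**
- Reported SE without strata = SD × sqrt(1-rho²) × sqrt(2/n). At rho = 0 this is 12 × sqrt(2/63) = 2.138.
- True SE under stratified allocation = reported SE × sqrt(1-q).
- Type I error = 2Φ(-1.96/sqrt(1-q)).
- Power as written = Φ((6 - 1.96 × reported SE)/true SE).
- Power with strata in the model = Φ(6/true SE - 1.96).

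Example at q = 0.10, rho = 0: true SE = 2.138 × 0.949 = 2.028. Power as written = Φ((6 - 4.191)/2.028) = Φ(0.892) = 81.4%. Power with strata = Φ(2.958 - 1.96) = Φ(0.998) = 84.1%.

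| q | SE too large by | Type I error | Power as written / with strata, rho = 0 | rho = 0.3 | rho = 0.5 |
|---|---|---|---|---|---|
| 0 | 0% | 5.0% | 80.1 / 80.1 | 83.7 / 83.7 | 90.0 / 90.0 |
| 0.05 | 2.6% | 4.4% | 80.7 / 82.1 | 84.3 / 85.5 | 90.6 / 91.4 |
| 0.10 | 5.4% | 3.9% | 81.4 / 84.1 | 85.0 / 87.3 | 91.1 / 92.7 |
| 0.20 | 11.8% | 2.8% | 82.8 / 88.1 | 86.4 / 90.8 | 92.4 / 95.2 |

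The power given up at rho = 0 is 0, 1.4, 2.7 and 5.3 points. It shrinks as the baseline correlation rises.

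**Step 3: check by simulation.** The formulas assume perfect balance within strata. A simulation relaxed this: 140 randomised, five centres × care setting × sub-sample (sub-sample only in Newcastle and Manchester), blocks of 4, 10% missing at random, rho = 0.3, 6,000 runs per setting. Block size, stratum frequencies and the sub-sample's sites are assumptions.

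| q | Type I error, as written / with strata | Power, as written / with strata |
|---|---|---|
| 0 | 5.2% / 5.3% | 82.4% / 82.3% |
| 0.05 | 4.7% / 5.2% | 83.2% / 84.0% |
| 0.10 | 3.7% / 4.7% | 84.1% / 86.2% |
| 0.20 | 3.6% / 5.1% | 84.9% / 89.2% |

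The Monte Carlo error is about 0.3 points for type I error (sqrt(0.05 × 0.95/6000)) and 0.5 points for power (sqrt(0.84 × 0.16/6000)). The direction agrees with step 2. The power differences are somewhat smaller, as expected when incomplete blocks and attrition leave some imbalance.

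**Step 4: cost in degrees of freedom.** Five centres need 4, care setting 1 and sub-sample 1, so 6 in total. With 126 analysed, residual degrees of freedom go from 126 - 3 = 123 to 117. The q = 0 row of the simulation shows no material penalty.

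**The case against.** The strongest defence is that this is a journal article, that it promises a full analysis plan, and that covariate lists are commonly left to such a plan. The article says that the model adjusts for baseline MADRS; it does not say that nothing else will enter. This stands in part: the unseen plan may already include the strata, in which case only the published statement needs correcting. It does not dispose of the point, because the article is not silent on covariates. It states the primary model and names its one covariate, and that model does not match the stated randomisation.

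The second defence is that the effect is conditional and small. This stands in full. At q = 0 nothing is lost, and no passage shows that the strata predict outcome. The age argument in particular is thin, since the sub-sample limit removes only the top five years.

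Two stronger readings are tempting. A reader might infer from the cut from 90% to 80% that the omission leaves the trial underpowered. The figures do not support this: the sample size never relied on strata adjustment, and the model as written has 80.1% to 82.8% power at rho = 0 and more at higher correlations. A reader might also infer that ignoring the strata invalidates the test. It does not: the error is on the conservative side and randomisation still protects the comparison.

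**Conclusion.** The point holds in conditional form. The stated primary model omits the factors used to stratify randomisation. If those factors are prognostic given baseline, the reported standard error is too large by up to about 12% over the assumed range of q, and by no more than about 5% for q up to 0.10. The corresponding power forgone is up to 5.3 points at q = 0.20 and under 3 points for q up to 0.10. If the factors are not prognostic, the two models perform alike.

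The size rests on q and rho, neither of which the documents give, and on near-complete balance within strata. The direction rests only on the stratified design. This is a minor to moderate matter of efficiency and of matching the analysis to the design. It should be changed because the gain is nearly free, not because the result would otherwise be unsound.

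**What to change.** State the primary model as week +5 MADRS regressed on arm, baseline MADRS, centre, care setting (primary or secondary) and mechanistic sub-sample (yes or no), all entered as main effects. Use the same stratification covariates, with each outcome's own baseline value, for the secondary continuous outcomes. If the factors are to be left out, give the reason.

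This takes one sentence in the protocol and one in the analysis plan, fixed before unblinding so that the choice of adjustment cannot be questioned afterwards. It needs no extra patients or data and uses about six of roughly 123 residual degrees of freedom.

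### Repeated measures ANOVA over all time points is a poor match to the objective of sustained response; name a mixed model with the week 24 treatment difference

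*Protocol article*

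**What the plan says.** The secondary clinical objectives include: "To assess whether the response is sustained for up to 21 weeks post cessation of metyrapone". Treatment ends at week 3, so this runs to week 24. The Follow-up section gives the visits: "Depression severity will be assessed using the MADRS administered by trained members of the research team at time +3, +5,+8, +16 and + 24 weeks". Table 2 adds a week 0 MADRS.

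Under Statistical analysis, the week 5 comparison has its own baseline-adjusted analysis: "The primary outcome will be an intention to treat analysis of variance of the MADRS scores of the two treatment groups". Persistence is handled separately: "The persistence of change in the MADRS score will then be assessed using repeated measures analysis of variance utilising data from all time points". The choice extends beyond the MADRS: "The change and persistence of the change in other clinical and quality of life measures will be examined using the same methods".

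The section names no treatment comparison at week 24 and no group-by-time term. It defers detail to a Study Analysis Protocol, to be written before unblinding, which is not available here.

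**The concern.** Persistence is a question about late visits: how large is the treatment difference at week 24? A repeated measures ANOVA yields two standard results. One is a group effect averaged over visits, and three of the five follow-up visits fall by week 8. The other is a group-by-time test, which asks only whether the difference between arms varies somewhere over time. A significant group effect with a non-significant interaction is easily read as a sustained response, yet it can arise when much of the benefit has gone.

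The classical form of the method also requires every score from every patient, so partial follow-up is lost. The article presents its long follow-up as a main strength of the trial, and the same method is to serve the other symptom scales and quality of life.

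**Working it through.** **The plan's own figure.** The section on sample size gives effect size 0.5, "assuming a post-intervention standard deviation of 12 points [33], corresponds to a six point difference on the MADRS", and 10% attrition. Two-sided, n per group = 2(z₀.₉₇₅ + z_power)² × 12² / 6².
- 80% power: 2(1.960 + 0.842)² × 144/36 = 62.8, so 63; 63/0.9 = 70.
- 90% power: 2(1.960 + 1.282)² × 144/36 = 84.1, so 85; 85/0.9 = 94.4, so 95.

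Both reproduce. They concern week 5; the article gives no figure for the persistence analysis.

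**Assumptions added here.** SD 12 at each visit (the plan's value), equal correlation ρ of 0.4 to 0.8 between visits, the fading patterns below, and intermittent misses of 2–3% per visit.

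**Complete profiles.** Share with all five follow-up scores = (1 − attrition)(1 − miss)⁵.
- 10% attrition, 2% misses: 0.90 × 0.98⁵ = 0.814, or 57 of 70.
- 10% attrition, 3% misses: 0.90 × 0.97⁵ = 0.773, or 54 of 70.
- If attrition were 15–25% instead: 0.85 × 0.98⁵ = 0.768 (54 of 70) to 0.75 × 0.97⁵ = 0.644 (45 of 70).

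**Formulas.**
- Group effect: SD of a five-visit mean = 12√[(1 + 4ρ)/5], which is 8.65, 9.90 and 11.0 at ρ = 0.4, 0.6 and 0.8; power from the noncentral t.
- Group-by-time: noncentrality = (n/2) × Σ(eᵢ − ē)² / [144(1 − ρ)], on 4 and 4(2n − 2) degrees of freedom; power from the noncentral F.

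**Abrupt loss: 6, 6, 6, 0, 0 points at weeks 3, 5, 8, 16, 24.**
- Mean effect 18/5 = 3.6 (18/6 = 3.0 if week 0 counts as a time point); Σ(eᵢ − ē)² = 43.2.
- Group effect at ρ = 0.6: significant 40% of the time at 45 per arm, 47% at 54.
- Group-by-time at ρ = 0.6: noncentrality 16.9 at 45 per arm and 20.3 at 54, so power 92–96%.

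**Gradual loss: 6, 6, 5, 4, 3 points, 54 per arm.**
- Mean effect 24/5 = 4.8; Σ(eᵢ − ē)² = 6.8.

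| ρ | Group effect significant | Noncentrality, interaction | Interaction power |
|---|---|---|---|
| 0.4 | 81% | 2.13 | 18% |
| 0.6 | 70% | 3.19 | 26% |
| 0.8 | 61% | 6.38 | 49% |

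Under equal correlation the two tests are independent. The chance of a significant group effect together with a non-significant interaction is therefore about 0.81 × 0.82 = 0.66, 0.70 × 0.74 = 0.52 and 0.61 × 0.51 = 0.31. In these cases half the benefit has gone by week 24.

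**What a week 24 contrast gives.** With 63 per group observed, the unadjusted 95% CI half-width is 1.96 × 12 × √(2/63) = 4.2 points, with 80% power for 6 points. For a remaining effect of 3 points the noncentrality is (3/12)√(63/2) = 1.40 and power is about 29%. The contrast does not create power, but its interval shows how little is known at week 24, which the averaged effect conceals.

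**The case against.** The strongest defence is that repeated measures ANOVA contains the tools needed. It has a group-by-time test and permits a contrast at any visit, and the article does not say that the group effect is the test of persistence. This largely stands. A reader might infer that the method cannot show whether the effect lasts to week 24, or that an effect that has vanished would be called persistent 40–47% of the time. The documents do not support either reading: in that same abrupt scenario the interaction test detects the loss 92–96% of the time. The defence is weaker for gradual loss, where the interaction is usually missed, and a non-significant interaction is not evidence of persistence in any case.

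A reader might also infer that the plan drops every patient with a missed visit. The article does not say so. Complete-case deletion belongs to the classical method, and missing-data handling may be in the unseen analysis plan. Losses of 15–25% also depart from the only stated figure, 10%. Nor is serious bias from selected completers shown. In one simulated missing-at-random scenario (118 of 140 complete, true week 24 difference −6), complete cases gave −6.2 (SD 2.15) and a likelihood analysis −5.9 (SD 2.07).

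Finally, the Intervention section asks clinicians to hold medication stable only up to week 5, so one might infer that later switching invalidates the late comparison. It does not: comparing arms regardless of later treatment is legitimate, concomitant medication is recorded, and a mixed model would not change this. It is not part of the point.

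Deferral to a later plan does not remove the point itself. The method of analysis is already stated, and the later plan would inherit it.

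**Conclusion.** The concern holds in a limited form. The article fixes a method that matches its persistence objective poorly, because neither of its standard results estimates the week 24 effect. Over ρ = 0.4–0.8, with the effect halved by week 24 and 54 patients per arm, the interaction has 18–49% power while the averaged group effect is significant 61–81% of the time. The classical form would also set aside roughly 13 to 16 of 70 patients per arm (70 − 57 and 70 − 54).

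These sizes rest on the assumed fading patterns, equal correlation, SD 12 at every visit and 2–3% intermittent misses; only the SD and the 10% attrition come from the document. The point concerns secondary outcomes. The week 5 analysis and the sample size are untouched. It should be corrected, since the remedy is cheap and long follow-up is a stated strength of the trial.

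**What to change.** In the Statistical analysis section, and in the analysis plan before unblinding, replace the repeated measures ANOVA with a likelihood-based mixed model for repeated measures:
- all available post-baseline scores (weeks 3, 5, 8, 16 and 24), with week 0 as a covariate and not as an outcome level;
- treatment-by-visit and baseline-by-visit terms;
- the stratification factors (mechanistic sub-sample, care setting, centre);
- an unstructured covariance.

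Define persistence as the treatment difference at week 24 with its 95% CI, with weeks 8 and 16 as supporting estimates. Use the same model for the other clinical and quality-of-life measures that the article places under the same methods.

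The cost is wording only: no new data, visits or patients, and no change to the primary analysis.
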